### Analysis of primary outcomes

Proportion of mothers whose births included birth companions will be reported and compared between intervention and standard care arms at the end of the intervention using cluster-weighted chi-square test [25, 27]. If the baseline data shows difference between intervention and standard care arms in covariates which may affect the outcome, such covariates will be adjusted for using logistic regression model with cluster-correlated standard error estimates to account for the correlation of outcomes within facility.

The model will include birth companion status at birth as the study outcome, study arm as the primary predictor, and adjustment for covariates that are differentially distributed between the study arms. The primary analysis will be conducted separately for each sub-national region.

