**Nasarawa**			
1	312	CEmONC	
2	300	CEmONC	
3	135	BEmONC	
4	109	CEmONC	
5	69	CEmONC	
6	64	BEmONC	
7	45	CEmONC	
8	41	CEmONC	
9	37	BEmONC	
10	37	BEmONC	
11	37	CEmONC	
12	36	BEmONC	

We will use a mixed methods approach to assess impact of the birth companion intervention package and measure the study outcomes with exit interviews, health facility register data extraction, in-depth interviews (IDIs), focus group discussions (FGDs), and key informant interviews (KIIs).

There are five data collection periods. We will first conduct a baseline assessment over the course of approximately four weeks, in facilities meeting the inclusion criteria. Health facilities that decline to participate in the study will be replaced by another facility. Facilities will be randomized after the baseline survey in a 3:1 ratio (i.e., for every three facilities that implement the birth companion intervention, one will serve as a control facility). Randomization is stratified by the number of facility deliveries and by country (Ethiopia) or by county or state within a country (Kenya and Nigeria). Intervention facilities will prepare to introduce the birth companion intervention package over the course of approximately two months to facilitate the presence of birth companions during labor, birth, and the postnatal period. Control facilities will continue to provide the local standard of routine care which may or may not include a birth companion. Facilities will not be replaced or reallocated to study arm post-randomization. This study does not place restrictions on facilities or participants regarding participation in other interventions or research.

We will have three quarterly quantitative and qualitative data collection periods, each lasting for approximately one week. We will conduct an endline quantitative survey, approximately 12 months after birth companion intervention initiation. Mothers, birth companions, health care providers, and unit managers in study facilities will have the option to decline to participate in the study.

At the end of the study, control facilities will be supported to implement the birth companion intervention package by staff from an intervention facility that has a birth companion coverage of approximately 50% or higher (see Fig. 2), assuming that one is available. We will provide limited technical and material support during this period.

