### Statistical analysis and power

The following methods will be used to describe group characteristics or differences: for categorical variables, the number, and percent in each category; for continuous variables, the mean, median, standard deviation, quartiles, and range (minimum, maximum). Adequacy of the randomization will be assessed at baseline by comparing characteristics of participants and facilities in intervention and control arms, including demographics, birth companion coverage, and experience of care.

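### Primary-outcome covariates are chosen by observed baseline imbalance, while the delivery-volume strata and facility baseline coverage are not fixed in the analysis

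*Protocol article*

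**What the plan says.** Under Analysis of primary outcomes, coverage is compared between arms "at the end of the intervention using cluster-weighted chi-square test". A logistic model with cluster-correlated standard errors then comes in on a condition: "If the baseline data shows difference between intervention and standard care arms in covariates which may affect the outcome". Its terms are given as "study arm as the primary predictor, and adjustment for covariates that are differentially distributed between the study arms". The section defines neither how large a difference must be nor how the two analyses rank. It also says that the primary analysis is done separately in each sub-national region.

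Under Design and setting, "Facilities will be randomized after the baseline survey in a 3:1 ratio", and "Randomization is stratified by the number of facility deliveries" as well as by country, county or state. Under Statistical analysis and power, "Adequacy of the randomization will be assessed at baseline by comparing characteristics of participants and facilities in intervention and control arms"; coverage and care experience are among the items listed for that check. Baseline coverage is therefore measured in every facility before allocation, but its stated use is to check the randomisation. Analysis of secondary outcomes repeats the imbalance rule for the continuous outcomes, which include the Person-Centered Maternity Care score.

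**The concern.** Covariates should be chosen for prognostic value and before the data are seen. Here a covariate that may affect the outcome enters only if the arms happen to differ on it. Baseline data precede allocation, so any such difference is chance, and with three control facilities per region chance differences can be large. Whether an adjusted estimate is produced, and with which terms, then varies from region to region with the draw.

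Two items with a design reason to be in the analysis are not fixed there. Delivery volume was a stratification factor; a test that ignores a prognostic stratum uses too large a standard error. Facility baseline coverage is the primary outcome measured earlier in the same facilities, and it can enter only if it looks unbalanced.

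**Working it through.** **1. The plan's own figure.** Inputs from Sample size: 20% v 50%, 62 women per facility (186 v 558), 3 v 9 facilities, coefficient of variation of cluster size 1, alpha 0.05 (two-sided assumed), ICC between 0.05 and 0.5. With ICC 0.05 the design effect is 1 + ((1 + 1) × 62 − 1) × 0.05 = 7.15, so the effective sizes are 186/7.15 = 26.0 and 558/7.15 = 78.0. The pooled proportion is 0.425.
- Null SE = √(0.425 × 0.575 × (1/26.0 + 1/78.0)) = 0.112
- Alternative SE = √(0.16/26.0 + 0.25/78.0) = 0.097
- Power = Φ((0.30 − 1.96 × 0.112)/0.097) ≈ 0.80

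The stated 80% reproduces at ICC 0.05 (also at ICC 0.10 with equal clusters, design effect 7.10, power 0.801). The calculation contains no strata and no covariates.

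**2. Size of chance imbalance.** SD of the between-arm difference in facility coverage = √(ICC × p(1 − p) × (1/3 + 1/9)).

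| ICC | p = 20% | p = 5% |
|---|---|---|
| 0.05 | 6 points | 3 points |
| 0.2 | 12 points | 6.5 points |
| 0.5 | 19 points | 10 points |

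The target effect is 30 points. The formula leaves out sampling of women within facilities, which raises the SD, and balancing by the volume strata, which lowers it if volume is prognostic.

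**3. What the trigger would do.** No threshold is given, so p < 0.05 is taken as an example. Counting five demographic items, coverage and experience of care as seven independent covariates, at least one is flagged by chance with probability 1 − 0.95^7 = 0.30 in a region and 1 − 0.95^35 = 0.83 somewhere in five regions. Yet in simulation (12 facilities, three assumed volume strata of four, 6,000 runs) baseline coverage itself was flagged in only about 0.5% to 3% of trials. A test-based trigger would nearly always leave it out. A judgement by eye could let in much more.

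**4. Ignoring the strata.** Same simulation, with r = 0.5 for the analysed facility values:

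| Strata share of between-facility variance | Quantity | Unadjusted | Stratum terms | Baseline term | Both |
|---|---|---|---|---|---|
| 20% | type I error | 2.8% | 4.9% | 4.8% | 5.0% |
| 20% | power | 0.44 | 0.53 | 0.61 | 0.58 |
| 50% | type I error | 0.6% | 4.8% | 4.4% | 4.9% |
| 50% | power | 0.41 | 0.74 | 0.78 | 0.77 |

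The spread of the estimate is the same with and without stratum terms (0.59 and 0.47 in the two settings). The gain comes from a correct standard error. Part of the baseline term's gain here arises because baseline coverage carries the stratum differences. A second simulation, with the Machakos volumes, gave a milder picture: type I error about 2–4% unadjusted against 4–5%, and power 0.48 against 0.64 when strata explain half the variance.

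**5. Baseline term alone, single region, Machakos volumes.** The protocol gives no r, so a range is shown.

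| Assumed r | Change in power |
|---|---|
| 0.3 | loss of about 3–4 points |
| 0.5 | about none |
| 0.7 | gain of about 1 to 11 points over ICC 0.05 to 0.20 (0.68 to 0.76 at ICC 0.10; 0.45 to 0.56 at 0.20) |

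A rough guide to the break-even: with 12 facilities a baseline term multiplies the variance of the estimate by (1 − r²) × 9/8, which equals 1 at r = 1/3 for the observed facility proportions. Small facilities give noisy proportions, so the underlying correlation must be higher than that.

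**The case against.** The first-named comparison, the chi-square test, has a fixed form. The trigger also requires that a covariate may affect the outcome, so it is not blind to prognosis, and baseline coverage is a candidate for it. Both points stand. They narrow the defect to an unranked pair of analyses, one of them data-driven.

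Four stronger readings are tempting and not supported:
- A reader might infer inflated false positives. Ignoring the strata makes the test conservative, so the loss is in power.
- A reader might infer that many covariates will flood a 12-cluster model. That depends on the unstated threshold, and woman-level covariates such as age or parity do not each cost a facility-level degree of freedom.
- A reader might infer a large, assured gain from a baseline term, especially in an analysis pooling all 60 facilities. The stated primary analysis is by region, and the regional gain depends on r. There are reasons to doubt a high r: assumed baseline coverage is only 5–20%, nine of 12 facilities receive a package meant to change coverage, and at 16 births a month seven days yield about four women (16 × 7/30 = 3.7), although the baseline survey runs about four weeks.
- A reader might infer that all baseline data are in hand. Trial status says that Nigeria's baseline survey was still being prepared.

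A separate analysis plan may list covariates. But the protocol does not leave the matter open: it states an imbalance rule.

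**Conclusion.** The point holds and should be corrected. The imbalance trigger, with no threshold and no ranking against the chi-square test, makes the reported estimate depend on chance differences among 12 facilities; this needs no assumption about r. The missing volume strata cost power to the extent that volume predicts coverage, which the protocol does not quantify; the figures above assume that strata explain 20% to 50% of between-facility variance. Region is already handled by separate analyses. The case for the baseline term is weaker: a modest loss, no change or a gain, depending on r. Its main merit is that the one covariate with a clear prior claim is fixed in advance. The unadjusted test is not shown to be invalid.

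**What to change.** Before any endline comparison by arm, drop the imbalance trigger and name one primary analysis per region. It should reflect the volume strata, by stratum terms or by re-randomisation within strata, include facility-level baseline companion coverage as the single pre-specified baseline covariate, and use a small-sample reference. Baseline coverage must enter as a facility value because the women differ between surveys. Label any other imbalance adjustment as sensitivity. Treat the arm comparison of the Person-Centered Maternity Care score the same way, with its facility baseline mean.

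Cost: wording only, as the baseline survey is already part of the design. Of the 10 facility-level degrees of freedom per region (12 − 2), the baseline term uses one. Stratum terms use one fewer than the number of strata, which the article does not give: two in total with two strata, three with three. Re-randomisation uses none for the strata but is coarse: three strata of four with one control each (an assumption) give 4 × 4 × 4 = 64 allocations and a smallest p-value of 1/64 = 0.016. If r is about 0.3, the baseline term costs about 3–4 points of power.

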### Sample size

#### Quantitative

The sample size justification is based on estimating coverage of birth companionship. We assumed a within-facility intra-class correlation coefficient (ICC) between 0.05 and 0.5 (higher is more reasonable). We also assumed post-birth companion support coverage at 50%. Baseline/standard practice birth companion coverage varied between 5% and 20%.

Sample size is calculated separately by country for two-sample comparison of proportions (with pooled Z-test) in a cluster randomized design using PASS (PASS 15 Power Analysis and Sample Size Software (2017). NCSS, LLC. Kaysville, Utah, USA, ncss.com/software/pass) [25].

The calculations below apply to the study area in Ethiopia, the two study counties in Kenya, and the two study states in Nigeria. We assume the same baseline level of birth companion coverage in all three countries. There are the same total number of facilities to be randomized at each study area, n = 12 (three in the standard arm and nine in the intervention arm). There will be a total of 12 facilities in Ethiopia, 24 in Kenya, and 24 in Nigeria.

The number of women per facility and total number of women across the two study arms per study site needed was calculated for at least 80% statistical power to test differences in proportions of birth companion coverage between study arms at 0.05 level of statistical significance, assuming that for every three facilities randomized to the birth companion intervention, one facility will be randomized to the standard practice arm and a coefficient of variation of one. Post-birth companion intervention coverage is assumed to be 50%.

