Conservatively assuming 20% birth companion coverage in the standard practice (control) arm and 50% in the birth companion intervention arm at the endline, to have 80% statistical power to detect this difference in proportions at 0.05 level of statistical significance, coefficient of variation of one, we will need to include 62 women who recently gave birth (on average) at each of the 12 health facilities per study area, for a total of approximately 744 women across the two study arms (186 in control arm, 558 in the intervention arm). In this scenario in each of the study sites (Addis Ababa and surrounding area, Machakos and Murang’a counties, and Nasarawa and Kano states), three facilities will be randomized to the standard arm, and nine facilities to the birth companion intervention arm. Since the coefficient of variation is almost one, based on the facility data presented in Tables 1, 2 and 3, the same sample size is used for considering a varying cluster size. We will include all births occurring within the seven data collection days from all facilities. Thus, we will recruit more births from health facilities with a higher volume of births and fewer from health facilities with smaller volume of births. Randomization of facilities was conducted by the Johns Hopkins Biostatistics Center.

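### With three unequal control facilities per site, the planned primary tests need a small-sample method; the usual large-sample versions reject too often, mildly for the chi-square and severely for the adjusted model

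*Protocol article*

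**What the plan says.** Under Analysis of primary outcomes, coverage is "compared between intervention and standard care arms at the end of the intervention using cluster-weighted chi-square test". If baseline covariates that may affect the outcome differ between arms, they are adjusted for in a "logistic regression model with cluster-correlated standard error estimates to account for the correlation of outcomes within facility". The same section runs the primary analysis separately in each sub-national region.

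The Sample size section (Quantitative) gives every study area "n = 12 (three in the standard arm and nine in the intervention arm"). All births in a seven-day window are taken, with the result that "Thus, we will recruit more births from health facilities with a higher volume of births and fewer from health facilities with smaller volume of births". The calculation there uses a pooled Z-test, an ICC between 0.05 and 0.5 with higher values called more reasonable, and a cluster-size coefficient of variation of one.

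Analysis of secondary outcomes uses similar methods for binary outcomes. For continuous outcomes it uses a cluster-weighted t-test and linear models with cluster-correlated standard errors.

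The article names no small-sample correction, degrees of freedom or reference distribution. It does not rule them out either.

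**The concern.** Cluster-robust standard errors, and chi-square tests adjusted for clustering, are justified when the number of clusters is large. Here the control arm has three, and sampling by volume lets one of them dominate. The control-arm variance is then estimated from very little replication and tends to come out too small, so p-values and intervals look more certain than they are.

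The stake is the trial's main claim. Each site gets its own test, and the results are meant to inform scale-up of the package.

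**Working it through.** **1. The plan's own figure.** Inputs from Sample size: 20% against 50% coverage, 186 control and 558 intervention women, mean cluster size m = 62, CV = 1, alpha 0.05 (taken as two-sided). The ICC behind 62 is not named. Try 0.05:

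- Design effect = 1 + ((CV² + 1)m − 1) × ICC = 1 + (2 × 62 − 1) × 0.05 = 7.15.
- Effective sizes: 186/7.15 = 26.0 and 558/7.15 = 78.0. Pooled proportion 0.425.
- Null SE = √(0.425 × 0.575 × (1/26.0 + 1/78.0)) = 0.112. Alternative SE = √(0.16/26.0 + 0.25/78.0) = 0.0967.
- Power = Φ((0.30 − 1.96 × 0.112)/0.0967) = 79.8%.

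The stated 80% is reproduced at the low end of the ICC range. ICC 0.10 without the CV term also gives it: design effect 1 + 61 × 0.10 = 7.1, power 80.1%. Both use a normal reference.

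**2. How much replication the control arm has.** The strata are not described beyond delivery volume. Assume three strata of four facilities by volume rank, with one control in each (4 × 4 × 4 = 64 allocations per site). Averaged over these, the largest control facility supplies 63-69% of control women, an effective 1.9-2.1 control clusters (1/Σw², where w is each facility's share of control women).

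**3. Why the plain sandwich is too small.** If control facilities share a common variance of their true coverage and sampling error is small beside it, the uncorrected sandwich recovers on average the fraction 1 − 2Σw³/Σw² + Σw² of the control-arm variance.

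- Three equal facilities: Σw² = 1/3 and Σw³ = 1/9, so the fraction is 1 − 2/3 + 1/3 = 0.67.
- An illustrative Ethiopian allocation from Table 1 (facilities 2, 6 and 10, with 262, 74 and 20 births a month): w = 0.736, 0.208, 0.056; Σw² = 0.588; Σw³ = 0.408. The fraction is 1 − 1.387 + 0.588 = 0.20.

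**4. False-positive rates.** Beta-binomial outcomes, no effect, coverage 20%, ICC 0.05-0.5, 744 women spread over the Table 1-3 volumes of all five sites, strata as in step 2, nominal 5%:

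| Method | Null rejection |
|---|---|
| Logistic, plain sandwich, normal reference | 25-34% |
| Same, with one facility-level covariate | 27-33% |
| Same, simple instead of stratified allocation | 23-31% |
| Same, 12 equal clusters of 62 | 16-23% |
| Logistic, K/(K−1) factor, t on 10 df | 18-26% |
| Logistic, Kauermann-Carroll correction, t | 11-15% |
| Logistic, Mancl-DeRouen correction, t, no covariate | 6-7% |
| Same, one covariate | 4-5% |
| Chi-square with estimated ICC (one reading of the cluster-weighted test) | 6-10% |
| Facility-level t-test, 10 df | 4-5% |

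A stratified permutation test, run for Ethiopia and Kano, gave 3.5-5.0%. Equal clusters with the K/(K−1) factor and t gave 11-17%, but volume-based recruitment will not produce equal clusters. At ICC 0.5 about 7% of data sets gave no usable logistic estimate and were left out of the sandwich rates.

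**5. Across five sites, taken as independent.** The chance of at least one false positive is 1 − (1 − a)⁵: 23% at a = 5%, 27-41% at 6-10%, and 76-87% at 25-34%.

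**The case against.** A reader might infer that the trial's primary analysis has a false-positive rate near 30%. The document does not support that, for three reasons.

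- The chi-square is the first comparison, and the logistic model is used only if baseline covariates differ. Under the reading tested, the chi-square's inflation is modest. Its exact form rests on cited references that are not at hand, so even 6-10% is conditional.
- The article does not say that the standard errors are uncorrected. That would be an inference from silence in a condensed article, and the full protocol or SAP may specify a correction. The same wording is compatible with anything from 4-7% to 34%.
- The rates also depend on assumed strata, ICC, coverage and cluster-size spread.

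All three stand, and they limit the claim. They do not remove it. The route to the logistic model may be well used: five demographic items are collected. If imbalance were judged by ordinary woman-level tests at 0.05 (an assumption), with five independent binary covariates at ICC 0.05 and the Ethiopian volumes, at least one would differ in about 93% of simulated trials. Nor would a general statement that clustering is handled settle the matter, because a K/(K−1) factor with a t reference still leaves 18-26%. The methods as named suit many clusters, and the design fixes few.

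**Conclusion.** The point holds conditionally. With nine against three facilities of very unequal size at each site, the large-sample versions of the named methods do not hold 5%: about 6-10% for the chi-square read as ICC-adjusted, and about 16-34% for the adjusted logistic model. Within that range, 25-34% applies to a plain sandwich with normal reference at the Table 1-3 volumes, and 16-23% to the same estimator with equal clusters. The figures assume 20% coverage, ICC 0.05-0.5 and, for the Table volumes, one control per volume third.

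It would go too far to say that at least one false success among the five sites is likely. That follows only if every site is judged by a large-sample logistic model. Under the chi-square reading the chance is 27-41%, against 23% for a test that holds 5%.

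This is more than a missing detail, because common software defaults applied to the named methods give a wrong error rate and the choice of correction decides validity.

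**What to change.** Before the endline analysis, name a primary per-site test that is valid for 12 clusters. Either of these serves:

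- endline coverage per facility, compared by a t-test or linear regression with degrees of freedom taken from the number of facilities; or
- a permutation test over the allocations that the stratified randomisation allowed. With 64 allocations, as assumed above, the closest attainable level is 3/64 = 4.7%.

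If the woman-level logistic model is kept, specify a Mancl-DeRouen-type bias-corrected sandwich with a t reference. It need not be demoted if that is done. Apply the same rule to the cluster-weighted t-test and the regression models for secondary outcomes. If the SAP already fixes such a method, the article's wording should be brought into line with it.

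The change is to analysis wording, but it has a price: wider intervals and lower nominal power than the large-sample test. Facility-level t-test power for 20% against 50% is about 83-88% at ICC 0.05, 63-68% at 0.10 and 18-21% at 0.5. The permutation test (Ethiopia and Kano) gave 77-84% at 0.05 and 58-62% at 0.10. It would therefore be wrong to say that the planned power is kept across the stated ICC range.

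Much of that loss belongs to the design and not to the test. The formula in step 1 of the working gives a design effect of 1 + 123 × 0.10 = 13.3 and power of about 50% at ICC 0.10. At ICC 0.5 it gives 1 + 123 × 0.5 = 62.5 and about 11%.

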### Data management

#### Quantitative data

Data collectors will receive in-depth training on the study objectives, procedures, and ethics by ACIPH, ICRHK, and MRHRC. A detailed manual with SOPs will be prepared and used in training, piloting, and research. The training will also include proper use of tablets and SurveyCTO, which will be used for data entry at the point of collection. There will be daily checks for completeness and consistency of the collected data. The electronic data capturing system will limit data inaccuracies by building in logic, range, and skip-patterns, and minimizing outliers. Investigators will also be supported with ongoing supervision visits from ACIPH, ICRHK and MRHRC.

Data will be de-identified after data collection by ACIPH, ICRHK, and MRHRC and shared with John Hopkins Biostatistics Center for multi-country analysis. De-identified data will be archived according to Bill & Melinda Gates Foundation policies on Synapse or a similar platform. We will also adhere to ACIPH, ICRHK and MRHRC data sharing policies.

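### The primary analysis is five separate 3 v 9 facility comparisons with no stated overall comparison, and the 80% regional power holds only near the bottom of the assumed ICC range

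*Protocol article*

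**What the plan says.** All references are to the protocol article.

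- **Question.** The Abstract (Background) describes one trial, asking whether a package that addresses known barriers can raise coverage of birth companions.
- **Randomisation.** Design and setting: "Randomization is stratified by the number of facility deliveries and by country" (Ethiopia), or by county or state in Kenya and Nigeria. Sample size gives 12 facilities per area, three control and nine intervention, in five areas: Addis Ababa and surroundings, Machakos, Murang'a, Kano and Nasarawa.
- **Sizing.** Sample size, Quantitative, uses a "two-sample comparison of proportions (with pooled Z-test) in a cluster randomized design" and asks for "at least 80% statistical power" to "test differences in proportions of birth companion coverage between study arms at 0.05 level of statistical significance". The scenario is "Conservatively assuming 20% birth companion coverage in the standard practice (control) arm and 50% in the birth companion intervention arm at the endline", with a cluster-size coefficient of variation (CV) of one. It yields 62 women per facility, or 744 per area. The ICC is put at "between 0.05 and 0.5 (higher is more reasonable". The value behind 62 is not given. The same section says sizing was done separately by country, although its figures are per 12-facility area.
- **Analysis.** Analysis of primary outcomes specifies a cluster-weighted chi-square test. If covariates differ at baseline, it adds a logistic model with study arm, those covariates and cluster-correlated standard errors. It then says: "The primary analysis will be conducted separately for each sub-national region".
- **Combined analysis.** The only hint is under Data management, where data are "shared with John Hopkins Biostatistics Center for multi-country analysis", with no outcome, model or status.

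**The concern.** The article fixes the level of the primary analysis, so this is not a detail left open. Splitting 60 randomised facilities into five sets of 12 has three consequences.

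1. Five results do not by themselves answer one question. If two or three regions reach significance, nothing stated tells the reader whether the package worked.
2. Each regional result rests on three control facilities. If facilities differ as much as the plan itself thinks likely, each test will usually miss a rise from 20% to 50%, and five inconclusive results could be read as failure of an effective package.
3. Cluster-robust standard errors from three clusters in one arm tend to be too small. An uncorrected test can then reject too often even though it is labelled 5%.

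**Working it through.** **Inputs.** From Sample size: coverage 20% v 50%; m = 62 women per facility, taken as stated; 3 v 9 facilities per region; alpha 0.05; CV 1; ICC 0.05 to 0.5. Sidedness is not stated, so two-sided is assumed. The design-effect formula is not stated, so two are shown.

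**Formulas.**
- Equal clusters: DE = 1 + (m − 1)·ICC.
- Unequal clusters: DE = 1 + [(1 + CV²)m − 1]·ICC.
- Effective size per arm = facilities × m / DE.
- Power = Φ[(0.30 − 1.96·SE_pooled)/SE_unpooled].

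**Reproducing the plan's 62.** Take equal clusters and ICC 0.10.
- DE = 1 + 61 × 0.10 = 7.1. Effective sizes are 186/7.1 = 26.2 and 558/7.1 = 78.6.
- Pooled proportion = (0.20 + 3 × 0.50)/4 = 0.425.
- SE_pooled = √[0.425 × 0.575 × (1/26.2 + 1/78.6)] = 0.1115.
- SE_unpooled = √(0.16/26.2 + 0.25/78.6) = 0.0964.
- Power = Φ[(0.30 − 0.2185)/0.0964] = Φ(0.845) = 80.1%, and 62 is the smallest m that reaches 80%.

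With CV 1 and ICC 0.05, DE = 1 + 123 × 0.05 = 7.15 and power is 79.8%. The stated figure is therefore reproduced, but only at an ICC of about 0.05 to 0.10.

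**Across the stated ICC range**, with all 60 facilities taken as 15 v 45 (930 v 2,790 women):

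| ICC | Region, CV 1 | Region, equal | All 60, CV 1 | All 60, equal |
|---|---|---|---|---|
| 0.05 | 80% | 97% | >99% | >99% |
| 0.10 | 50% | 80% | >99% | >99% |
| 0.20 | 27% | 51% | 92% | >99% |
| 0.30 | 18% | 35% | 77% | 97% |
| 0.50 | 11% | 22% | 53% | 85% |

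**More women cannot repair this.** With 3 v 9 facilities, equal clusters and unlimited women, power tops out at 78% for ICC 0.12, 54% for 0.20 and 22% for 0.50.

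**Type I error with three control clusters.** I simulated an uncorrected robust Wald test of two proportions under no effect. The assumptions are mine: beta-binomial outcomes, 20% coverage, lognormal facility sizes with CV 1 and mean 62, ICC 0.05 to 0.5. It rejected in about 22–25% of trials with 3 v 9 facilities and about 10–11% with 15 v 45, against a nominal 5%. Pooling helps, but a correction is needed in either case.

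**Five tests together.** If all five nulls are true, the chance of at least one false positive in either direction is 1 − 0.95⁵ = 22.6%. For false claims of benefit only it is 1 − 0.975⁵ = 11.9%. If each region truly had 80% power, all five would succeed with probability 0.8⁵ = 33%.

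**Strata.** Separate regional analyses condition on region. Birth volume, the other stratification factor, is not in the model as described and would enter only if it happened to differ at baseline.

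**The case against.** The strongest reply is that the regional analysis is deliberate. Each area was sized on its own. The Background reports very different starting points in the three countries, and the Discussion paragraph of the Abstract stresses varied settings. Region-specific answers are a legitimate aim, and demoting them, or adjusting them for multiplicity, is a trade-off. That stands.

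A reader might infer that the trial carries a family-wise error of about 23%. The document does not support this. The figure is a trial-wide error only if any single significant region counts as success, and no such rule is stated. As five questions in separate facilities, each has its own nominal 5%. Nor does the plan ignore its randomisation groups, since region is fully respected and only birth volume is left out.

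A reader might also conclude that no overall analysis will be done. All that can be said is that none is stated; a multi-country analysis is mentioned, and a separate analysis plan may define it. The same plan may hold a small-sample correction, so the simulation shows the cost of omitting one and does not show that it will be omitted.

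Finally, 20% control coverage is the plan's conservative end. At 5%, with a relative-efficiency correction for CV 1, regional power is 93%, 77% and 48% at ICC 0.20, 0.30 and 0.50. That softens the shortfall but does not remove it.

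**Conclusion.** The point holds as a fault of specification and of power. The article defines five primary comparisons, states no overall one, and gives no way to read five results together. The claim of 80% regional power is true only at an ICC of about 0.05 to 0.10. At ICC 0.20 and 0.50 regional power is 27–51% and 11–22%, against 92% to over 99% and 53–85% for all 60 facilities.

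This rests on a two-sided 0.05 test, the stated 20% v 50% and 62 women per facility, and an ICC common to all regions. The 60-facility figures also assume a similar effect everywhere. The ranges reflect the choice between equal clusters and full CV inflation, which the article does not settle. The small-sample point and the omitted birth-volume stratum are secondary but belong to the same rewrite.

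**What to change.** 1. Pre-specify one comparison of all 60 facilities at two-sided 0.05 as the overall answer, stratified by region and birth volume, with a named small-sample correction for clustering.
2. Keep the five regional estimates with confidence intervals and add an arm-by-region interaction. Apply the same correction to any regional test.
3. Say what a regional result may claim. If significance in any one region is to count as trial success, multiplicity control is needed. Bonferroni at 0.01 would leave about 55% power per region even at the ICCs that reproduce 62 women.
4. Restate regional power by ICC, naming the ICC and design-effect formula behind 62.
5. Reconcile the by-country wording in Sample size with the sub-national analysis.

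The cost is analysis wording, with no new facilities, women or data items. Trial status says recruitment is under way, so the change should be dated and made before endline results by arm are seen. The small downside is that the overall result averages over regions that may differ, which the regional estimates and the interaction would show.
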